#### Unblinding after the study

When the trial is completed, the data are locked and cannot be changed after verification; then, the unblinding process will be conducted. The unblinding process will be authorized by the researchers, operated by the IWRS administrators, and the blind bottom will be transferred to the sponsors.

### Intervention

#### Trial treatment methods

After randomization, the participants will be categorized into two groups receiving either XBJ injection (specification, 10 mL/piece; packaging, 10 pieces/container) or placebo (0.9% NaCl injection, suggested specification, 200 mL). XBJ injection is provided and manufactured by Tianjin Chase Sun Pharmaceutical Co., Ltd., Tianjin, China (lot number Z20040033). The 0.9% NaCl injection is provided by each sub-center. Both groups will receive routine medication according to the GOLD 2016 guideline [17].

The treatment group will receive routine medication plus XBJ injection every 12 h (q12h) for 60 min; a total of 50 mL XBJ will be diluted to 150 mL using 100 mL of 0.9% NaCl injection. The control (placebo) group will receive routine medication plus 0.9% NaCl injection (dosage 150 mL, q12h for 60 min). The dosage and speed of injection for the placebo and XBJ injection groups (150 mL, q12h, intravenous drip for 60 min) will be identical. The patients will receive the research medication within 24 h of enrollment, and the treatment period is 5 days.

#### Precautions

The following precautions will be observed:The use of other injections simultaneously during the course of intravenous infusions is prohibited.Other injections should be separated into 50 mL 0.9% NaCl.Prohibited medicines include ulinastatin, and TCM injections, such as Tanreqing, Reduning, and Qingkailing with efficacy similar to that of XBJ.The routine treatment of AECOPD should be carried out simultaneously, and XBJ injection should not be used as a substitute.If medication is administered for < 5 consecutive days and the patients’ clinical symptoms improve significantly resulting in discharge or the condition deteriorates, necessitating other treatments, the administration of the research medication will be suspended. The data for the first day of withdrawal will be recorded to day 6, and the follow up will be continued until day 28.

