#### Emergency unblinding

The patient’s group allocation should be known in the event of an emergency and can be obtained from the drug administrators. Researchers should contact the principal within 24 h to report the reasons for unblinding. The precise cause of unblinding, the date of the emergency, the treatment situation, and the results must be reported in the CRF. After unblinding, the case will be withdrawn and the data will be recorded to day 6 of the trial evaluation.

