#### Secondary outcome measures

The secondary outcome measures will be:Changes in immune indicators (detected by flow cytometry).Changes in inflammation indicators (detected by enzyme-linked immunosorbent assay).Respiratory support: the duration of oxygen therapy, high-flow humidification oxygen therapy, noninvasive mechanical ventilation, and invasive mechanical ventilation.Mortality rate after 28 days.Blood gas analysis (including blood lactate).Improvement in acute physiology and chronic health evaluation II (APACHE II) scores; the evaluation of improvement is based on differences in the APACHE II scores before and after the intervention.Improvement in clinical symptoms based on improvement in dyspnea, cough, sputum, and the use of accessory respiratory muscles (using the scoring system shown in Table 2). According to the differences in the scores before and after the intervention, the evaluation criteria are as follows:Significantly effective: the score decreased ≥ 3;Effective: the score decreased from 1 to 3;Ineffective: no change in the score;Exacerbation: the score increased ≥ 1;Name, dosage, and duration of antibiotic use.Name, dosage, and duration of corticosteroid use.Changes in laboratory inspection indicators.Incidence of complications.Length and cost of intensive care unit (ICU) stay.Length and cost of hospitalization.

**Table 2 Tab2:** The clinical symptoms scoring system of AECOPD

Score	Dyspnea	Cough	Sputum production	Use of accessory respiratory muscles
0	–	No cough	No sputum	No neck muscle tension and periodic contraction
1	Shortness of breath when flat on the ground or walking up one floor level	Intermittent cough, but no symptoms at night	Sputum volume ≤ 30 mL the whole day and night	Neck muscle tension, but no obvious muscle activity
2	Shortness of breath when walking with peers	Sometimes cough, which probably affects sleep	Sputum volume ≥ 30 mL and ≤ 50 mL	Visible slight contraction of the neck muscles
3	Need to stop so as to breathe when walking at their own speed	Frequent cough affecting sleep	Sputum volume ≥ 50 mL and ≤ 100 mL	Moderate contraction of the neck muscles, not with clavicular fossa and intercostal retraction
4	Shortness of breath when dressing or undressing	–	Sputum volume ≥ 100 mL	Strong contraction of the neck muscles, with abdominal contradictory movement

The evaluation criteria for the improvement in clinical symptoms is according to the total scores of the 4 items

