### Follow up

Various parameters are followed up according to the data collection time points (Fig. 2).Screening period (1 day): 24 h before recruitment.Intervention period (5 days): follow up and recording of data every dayPeriod after intervention (within 28 days after treatment): follow up on days 6 and 28. If the patient is discharged, contact is established via telephone or a short messaging service.

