### Safety and adverse events monitoring

In this trial, safety will be monitored by an independent data safety and monitoring board (DSMB) team comprising clinical physicians, evidence-based medicine experts, and statisticians. The safety assessment with respect to the vital signs, routine blood and urine tests, hepatic and renal function, fecal occult blood test, and electrocardiogram results will be conducted at every visit to avoid adverse events (AEs).

The DMSB assigns the severity of AEs as mild, moderate, severe, or serious adverse events (SAEs). Any AEs that occur during the study process should be recorded in the AEs form, including the time, severity, and duration of the AEs, the measures adopted, and the outcomes. These AEs will be addressed appropriately, and the treatment measures and results will be recorded. The subjects with AEs will be followed up. The mild AEs and SAEs are followed up until the adverse reactions disappear and the laboratory indicators return to the normal or the baseline level.

The relationships of AEs to the research medication are assessed as “impossible”, “suspicious”, “possible”, “probable”, or “definite” by the DMSB. The causal judgment indicators include whether the administration time and the suspected AEs exhibit a reasonable relationship; whether the suspected AEs fulfill the criteria for the typical reactions of the drug; whether the AEs can be explained by the effects of the combined drug, patient’s clinical condition, or other therapies; whether the suspected adverse reactions disappear or are mitigated after discontinuation of the drug; and fwhether the same reaction recurred after repetitive administration of the research medication.

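### Patients who stop study drug early have their withdrawal-day data filed under day 6, so secondary before-after outcomes are read at a time that depends on how the patient did

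*Protocol article*

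**What the plan says.** All references are to the protocol article.

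- **Trial treatment methods:** "The patients will receive the research medication within 24 h of enrollment, and the treatment period is 5 days".
- **Precautions:** the rule applies when study drug is given for fewer than 5 consecutive days and "clinical symptoms improve significantly resulting in discharge or the condition deteriorates, necessitating other treatments, the administration of the research medication will be suspended". It continues: "The data for the first day of withdrawal will be recorded to day 6, and the follow up will be continued until day 28".
- **Emergency unblinding** has a parallel wording: "the case will be withdrawn and the data will be recorded to day 6 of the trial evaluation".
- **Follow up:** data are recorded daily during the 5 intervention days, followed by "follow up on days 6 and 28". It adds: "If the patient is discharged, contact is established via telephone or a short messaging service".
- **Secondary outcome measures:** for APACHE II, "the evaluation of improvement is based on differences in the APACHE II scores before and after the intervention". The symptom categories are also built on a before-after score difference. Neither names the day of the later reading, and no day is given for blood gas, immune or inflammatory markers.
- **Statistical analysis:** the full analysis set (FAS), used for the main analysis, keeps anyone who received at least one treatment. Missing data are left to an unnamed imputation method.
- **Withdrawal or dropout criteria:** patients with under 5 days of drug are left out of the analysis unless they went home improved or died of their illness. Patients given other specific treatment after a change in condition are also left out.

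**The concern.** An exacerbation normally resolves over days in both arms, so the day of the second reading helps to determine the size of a before-after change. Under the Precautions rule that day is not fixed. A patient who completes treatment is read on day 6. A patient who goes home on day 3 contributes a day-3 value as the day-6 value. A patient who deteriorates on day 2 contributes a day-2 value, although that patient may well still be in hospital on day 6 and could be measured then.

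The reason for stopping is improvement or deterioration, which is what the outcomes are meant to measure. If Xuebijing (XBJ) changes who goes home early or who deteriorates, the two arms are read at different points of the illness, and part of any difference between them reflects timing.

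The outcomes concerned are secondary, but one of them matters more than its label suggests. The Objectives section lists the effect on regulatory T lymphocytes as a primary objective, and the immune markers behind it are exposed wherever they are read at day 6.

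**Working it through.** The plan states no figure on this point. The check is therefore a reading of the text followed by an illustration on assumed inputs.

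**Step 1: what the rule means.** Two readings are possible.

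- *Assignment:* the values of the first withdrawal day are entered as the day-6 evaluation. Three things favour this. The sentence speaks of the data of a single day. The emergency-unblinding sentence uses the same construction and names the day-6 evaluation. The Follow up section makes day 6 the first visit after treatment.
- *Continuation:* recording goes on from withdrawal through day 6. Deteriorating patients still in hospital would then be read correctly. For discharged patients the article offers only telephone or short-message contact, which cannot supply a blood gas or flow cytometry result. Their day-6 laboratory values would be missing.

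Assignment is the more natural reading, but sites could apply either.

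**Step 2: how far the reading day can move.** With 1 to 4 completed days of drug, the first day off drug is day 2 to day 5. The reading is therefore k = 6 − 5 = 1 to k = 6 − 2 = 4 days early.

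**Step 3: early improvers.** Let r be the further recovery per day after stopping, and p the share of an arm that stops early through improvement.

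- Under-reading of an arm's mean change = p × k × r.
- Shift in the between-arm difference, against the arm with more early improvers = (difference in p) × k × r.

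All inputs are assumptions, with r = 1 APACHE II point per day:

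| Early improvers, XBJ vs control | k = 1 | k = 4 |
|---|---|---|
| 10% vs 10% | 0 | 0 |
| 20% vs 10% | 0.10 × 1 = 0.1 | 0.10 × 4 = 0.4 |
| 30% vs 10% | 0.20 × 1 = 0.2 | 0.20 × 4 = 0.8 |

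With equal shares and equal timing the shift cancels.

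**Step 4: deteriorating patients.** Let d be the APACHE II score at withdrawal minus the score the patient would have on day 6. With assumed shares of 15% in control and 5% in XBJ, the shift is (0.15 − 0.05) × d = 0.10 × d. If the patient recovers by day 6, d is positive: at d = 6 the shift is 0.6 points in favour of XBJ. If the patient is worse still on day 6, d is negative: at d = −6 the shift is 0.6 points against XBJ. Nothing in the documents fixes the sign of d.

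**Step 5: which outcomes are touched.** The Abstract places the intubation rate and mortality at 28 days, and the Precautions sentence itself continues follow-up to day 28 after early stopping. Neither uses the day-6 value.

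**The case against.** The strongest defence is that the rule defines an end-of-treatment reading. For a completer, day 6 is the first day off drug; for an early stopper, the first withdrawal day is the same milestone. The outcome is defined as before versus after the intervention, not at a calendar day, so both groups are read at the end of their own treatment. This explains why the rule was written. It does not remove the problem, because the end of treatment comes earlier for patients whose course was better or worse, and the comparison still mixes treatment effect with time.

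Three further objections are fair. Daily data are recorded during treatment, and nothing says true dates are discarded, so the raw material for a better analysis may exist. The numbers above are assumptions throughout, and the improver example supposes continued recovery in patients already well enough to leave. Treating early-discharge values as missing also leaves missingness that depends on outcome. That last point stands as a cost, though the gap would be visible and could be modelled from the recorded course.

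A reader might go further and infer three things that the documents do not support:

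- *That day-28 laboratory values come only from patients still in hospital.* The safety section does say that tests including "fecal occult blood test, and electrocardiogram results will be conducted at every visit", and discharged patients are contacted remotely. But the assessment schedule (Fig. 2) is not shown, and no visible text places these efficacy laboratory outcomes at day 28.
- *That carrying forward deteriorating patients' values flatters XBJ.* Step 4 shows the sign is open. In addition, the Withdrawal or dropout criteria would drop patients given other treatment, so where that exclusion is applied their values do not enter at all.
- *That the primary result is biased.* Step 5 rules this out for patients who stop early under the Precautions rule.

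**Conclusion.** The point holds for secondary before-after outcomes read at day 6: APACHE II, the symptom score and, if scheduled for that day, blood gas, immune and inflammatory markers. On the more natural reading, the rule gives completers and early stoppers different reading days that depend on outcome, within an analysis set that keeps both.

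If the arms differ in early discharge, the arm with more early improvers has its recovery under-read. For deteriorating patients the direction is unknown. The size cannot be computed from the documents. The 0.1 to 0.8 points for improvers illustrates unequal shares at 1 point per day and is not an estimate. The conclusion rests on the assignment reading, on recovery continuing after stopping, and on shares or timing differing between arms.

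A related contradiction adds to the uncertainty. The Withdrawal or dropout criteria leave out patients given other treatment after a change in condition, while Precautions and the FAS definition keep them. Which early stoppers contribute a day-6 value therefore depends on which section is followed.

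The change is worth making, but this is a matter of secondary outcomes and data recording.

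**What to change.** 1. Replace the Precautions sentence on data recording with: *Assessments on the day study drug stops are recorded under their actual study day; patients still in hospital have the scheduled day-6 assessment whether or not they are on study drug.* Keep the statement that follow-up continues to day 28.
2. Analyse these outcomes by actual study day, using the values recorded on days 1 to 5 (for example, a repeated-measures model). Treat day-6 values after early discharge as missing, and carry the withdrawal-day value forward only as a sensitivity analysis.
3. State the day of the later reading for each before-after outcome.
4. Apply the same recording rule to the day-6 wording under Emergency unblinding.
5. Reconcile the exclusion of patients given other treatment (Withdrawal or dropout criteria) with Precautions and the FAS definition.

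The cost is case report form and analysis wording. No visit is added, because day 6 is already a follow-up point and the patients concerned are inpatients. The downside is some missing day-6 values for early discharges, whose handling rests on a missing-data assumption that must be stated. The change should be made before data lock.

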#### Routine medication for AECOPD

Routine medication for AECOPD will be administered follows:Both groups will receive routine medication according to the GOLD 2016 guideline, including oxygen therapy, antibiotics, bronchodilators, corticosteroids, fluid balance administration, nutritional support, thromboprophylactic measures, and ventilatory support.Indications for invasive mechanical ventilation: - patients meeting any of the following conditions can be provided invasive mechanical ventilation: inability to tolerate noninvasive mechanical ventilation (NIV); failure of NIV; respiratory or cardiac arrest; respiratory pauses with loss of consciousness or gasping for air; diminished consciousness; psychomotor agitation inadequately controlled by sedation; massive aspiration; persistent inability to remove respiratory secretions; heart rate < 50 bpm with loss of alertness; severe hemodynamic instability without response to fluids and vasoactive drugs; severe ventricular arrhythmias; or life-threatening hypoxemia in patients unable to tolerate NIV.Systemic glucocorticoid therapy may cause interference in the results of this study, and hence, the following regulations for the usage of hormones were proposed:Whether or not to use glucocorticoids is determined by the researchers according to the patients’ condition;If needed, a dose of 40 mg prednisone per day for 5 days is recommended according to the GOLD 2016 guideline; if the dosage or duration is exceeded, this is recorded;If the symptoms are exacerbated after glucocorticoid withdrawal, it can be used again;The cumulative dose and time of glucocorticoid use during the 28 days needs to be recorded.

### Outcome measures

#### Primary outcome measures

The primary outcome of this study will be the endotracheal intubation rate. Endotracheal intubation has been commonly used in clinical practice and is associated with successful recovery of the breathing function [29]. However, the intubation process is also associated with significant risks of ventilator-acquired pneumonia, barotrauma, and failure to wean from spontaneous ventilation [30, 31]. It likely reflects the severity of AECOPD, the patient’s length of hospital stay, and mortality [32, 33]. Intubation indications were defined by a set of objective criteria [17], avoiding the inconsistencies associated with intubation on clinical grounds. The formula for evaluation is as follows:$$ \mathrm{Endotracheal}\ \mathrm{intubation}\ \mathrm{rate}=\left(\mathrm{the}\ \mathrm{number}\ \mathrm{of}\ \mathrm{endotracheal}\ \mathrm{intubation}\ \mathrm{cases}\right./\left.\mathrm{total}\ \mathrm{number}\ \mathrm{of}\ \mathrm{cases}\right)\times 100\% $$

#### Secondary outcome measures

The secondary outcome measures will be:Changes in immune indicators (detected by flow cytometry).Changes in inflammation indicators (detected by enzyme-linked immunosorbent assay).Respiratory support: the duration of oxygen therapy, high-flow humidification oxygen therapy, noninvasive mechanical ventilation, and invasive mechanical ventilation.Mortality rate after 28 days.Blood gas analysis (including blood lactate).Improvement in acute physiology and chronic health evaluation II (APACHE II) scores; the evaluation of improvement is based on differences in the APACHE II scores before and after the intervention.Improvement in clinical symptoms based on improvement in dyspnea, cough, sputum, and the use of accessory respiratory muscles (using the scoring system shown in Table 2). According to the differences in the scores before and after the intervention, the evaluation criteria are as follows:Significantly effective: the score decreased ≥ 3;Effective: the score decreased from 1 to 3;Ineffective: no change in the score;Exacerbation: the score increased ≥ 1;Name, dosage, and duration of antibiotic use.Name, dosage, and duration of corticosteroid use.Changes in laboratory inspection indicators.Incidence of complications.Length and cost of intensive care unit (ICU) stay.Length and cost of hospitalization.

**Table 2 Tab2:** The clinical symptoms scoring system of AECOPD

Score	Dyspnea	Cough	Sputum production	Use of accessory respiratory muscles
0	–	No cough	No sputum	No neck muscle tension and periodic contraction
1	Shortness of breath when flat on the ground or walking up one floor level	Intermittent cough, but no symptoms at night	Sputum volume ≤ 30 mL the whole day and night	Neck muscle tension, but no obvious muscle activity
2	Shortness of breath when walking with peers	Sometimes cough, which probably affects sleep	Sputum volume ≥ 30 mL and ≤ 50 mL	Visible slight contraction of the neck muscles
3	Need to stop so as to breathe when walking at their own speed	Frequent cough affecting sleep	Sputum volume ≥ 50 mL and ≤ 100 mL	Moderate contraction of the neck muscles, not with clavicular fossa and intercostal retraction
4	Shortness of breath when dressing or undressing	–	Sputum volume ≥ 100 mL	Strong contraction of the neck muscles, with abdominal contradictory movement

The evaluation criteria for the improvement in clinical symptoms is according to the total scores of the 4 items

*AECOPD* acute exacerbation of chronic obstructive pulmonary disease

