### Sample size

A previous study [27] by the Collaborative Research Group of Noninvasive Mechanical Ventilation for COPD showed that the tracheal intubation rate in the routine treatment group (171 cases) was 15.2%, while it was 4.7% in the group receiving early noninvasive positive pressure ventilation plus routine treatment (171 cases). According to the literature, presuming that the rate of tracheal intubation in the XBJ group was reduced from 15.2% to 4.7%, the sample size was calculated according to the parameters α = 0.05 (two-sided test) and β = 0.2. Comparing the rates of the two groups with respect to the sample size estimation formula, we calculated that 127 patients should be recruited in each group. Considering an attrition rate of < 15%, the eligible participants in each group should be > 149. Therefore, we determined that the sample size should be 150 in each group (*n* = 300 in total).

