### Statistical analysis

An independent professional statistician and researcher will develop a complete statistical analysis plan for the trial, prior to the final analysis. The statistical analysis will be performed by the statistician in a blinded manner using the Statistical Analysis System (SAS) software version 9.2. The main analysis will be based on the full analysis set (FAS). According to the intention-to-treat principle, the FAS refers to a set of data on any participants who randomly receive at least one treatment. The per-protocol set (PPS), a subset of the FAS, includes data on only those participants who completed the trial without any violations of or deviations from the protocol. The FAS and PPS will be used for the assessment of efficacy. For the safety assessment, the safety set (SS) will be used, which includes patients who have received at least one safety evaluation after treatment.

All data, including the number of subjects included, drop-outs, elimination conditions, demographics, baseline characteristics, and efficacy and safety assessment, will be analyzed using different approaches. Descriptive and univariate statistics will be used to characterize the study participants and compare the baseline characteristics between the two groups. The primary outcome is the rate of endotracheal intubation, which will be determined by the Cochran-Mantel-Haenszel (CMH) test in the FAS population. We prefer to use the CMH chi-square test because it can deal with confounders of multi-center effects. Two-sided tests will be performed for all the other statistical analyses. The CMH chi-squared test or Fisher’s exact test will be used for comparing the categorical outcomes. The continuous outcomes will be analyzed by Student’s *t* test, while the AEs will be presented using descriptive statistics and compared using a chi-square test. A *P* value <0.05 will be considered to indicate statistical significance. Missing data will be explored and adjusted using the imputation method.

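### Raw noninvasive ventilation time is compared by t test although intubation, the primary outcome, can cut it short, so the comparison can be biased against an effective drug

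*Protocol article*

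**What the plan says.** Four places in the protocol article bear on this.

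- **Secondary outcome measures** has one respiratory-support item with four device-specific durations: "Respiratory support: the duration of oxygen therapy, high-flow humidification oxygen therapy, noninvasive mechanical ventilation, and invasive mechanical ventilation". The article gives no time window for them and no rule for patients who are intubated or die.
- **Statistical analysis** fixes the test: "The continuous outcomes will be analyzed by Student’s *t* test". It adds that "Missing data will be explored and adjusted using the imputation method".
- **Routine medication for AECOPD** names, among the indications for invasive ventilation, "inability to tolerate noninvasive mechanical ventilation (NIV); failure of NIV".
- **Primary outcome measures** states: "The primary outcome of this study will be the endotracheal intubation rate". **Sample size** sets the expected effect by "presuming that the rate of tracheal intubation in the XBJ group was reduced from 15.2% to 4.7" per cent.

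The article also says that an independent statistician and researcher "will develop a complete statistical analysis plan for the trial, prior to the final analysis". That plan is not available here.

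**The concern.** On a duration of support, a lower value is naturally read as better. NIV time, however, can end in two opposite ways: the patient recovers and comes off it, or the patient fails it and is intubated. A patient intubated after half a day of NIV contributes 0.5 days. A patient who recovers without a tube after 5 days contributes 5. On the raw scale the first patient has the better result.

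The event that produces the short value is the trial's own primary failure, and the design expects it to be about three times as frequent in the control arm. Each intubation that XBJ prevents can then replace a short NIV time by a longer one. The primary outcome could favour XBJ while NIV duration points the other way. If XBJ raised the intubation rate, the same mechanism could flatter it. The problem lies in the outcome and test as stated. It concerns survivors as well as deaths, so a rule for deaths alone would not cure it.

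**Working it through.** **1. The plan's own figure.** Inputs from Sample size: 15.2% and 4.7%, with "α = 0.05 (two-sided test) and β = 0.2". The mean rate is 0.0995 and the difference 0.105. The usual two-proportion formula with pooled variance under the null gives

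n = [1.96 × √(2 × 0.0995 × 0.9005) + 0.8416 × √(0.152 × 0.848 + 0.047 × 0.953)]² / 0.105² = (0.8297 + 0.3508)² / 0.011025 ≈ 126.4, so 127 per group.

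This matches the article, and 127 / 0.85 = 149.4 leads to 150. The sample size is not in dispute; only its rates are used below.

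**2. Expected intubations.** Control: 150 × 0.152 = 22.8. XBJ: 150 × 0.047 = 7.05. The difference is about 16 patients per 150.

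**3. Shift in mean NIV time.** The article gives no NIV durations, so these are assumptions. Let D be mean NIV days if not intubated, t mean NIV days before intubation, and r mean NIV days after extubation (0 if NIV is not resumed). Assume equal NIV need in both arms, no other effect of XBJ on NIV time, and every intubated patient first on NIV. The mean in an arm with intubation rate p is p(t + r) + (1 − p)D, so

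XBJ minus control = (0.152 − 0.047) × (D − t − r) = 0.105 × (D − t − r).

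With r = 0:

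- D = 5, t = 2: 0.105 × 3 = 0.32 days
- D = 5, t = 0.5: 0.105 × 4.5 = 0.47 days
- D = 7, t = 1: 0.105 × 6 = 0.63 days
- D = 8, t = 0.5: 0.105 × 7.5 = 0.79 days

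All are longer with XBJ, that is, apparently against it.

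**4. How far the sign depends on the assumptions.** Take D = 7 and t = 1.

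- r = 2: 0.105 × 4 = 0.42 days
- r = 4: 0.105 × 2 = 0.21 days
- r = 6: zero
- r = 8: 0.105 × (−2) = −0.21 days, now in favour of XBJ

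If only a share f of the prevented intubations concerns patients on NIV, and the others would have had no NIV either way, the shift is multiplied by f. With f = 0.5 and r = 0, 0.63 becomes 0.32 days.

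**5. What the t test would do.** Simulation with 150 per arm, all on NIV, and potential duration with mean 7 and SD 4 days, equal in both arms:

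| Scenario | Mean difference (days) | Significant against XBJ | Significant in favour |
|---|---|---|---|
| Intubation does not affect NIV time | 0.01 | 2.4% | 2.0% |
| NIV stops 0–2 days in if intubated, not resumed | +0.63 | 25% | 0.1% |
| As above, resumed for a mean of 8 days | −0.20 | 0.8% | 7% |

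**6. Size of true benefit hidden.** With r = 0, XBJ must shorten NIV among non-intubated patients by s = 0.105 × (D − t) / 0.953 merely to bring the raw difference to zero. For D = 7 and t = 1, s = 0.63 / 0.953 = 0.66 days, or 9.4% of D. For D from 5 to 10 and t from 1 to 2 days it is about 7–10%.

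**7. The alternative scale.** Let V be mean invasive days. Leaving deaths and the 28-day cap aside, the difference in days free of NIV or invasive ventilation is 0.105 × (t + V + r − D). With V = 10 (assumed) and r = 0, it is 0.105 × 2.5 = 0.26 days for D = 8 and t = 0.5, and 0.105 × 7 = 0.74 days for D = 5 and t = 2, both in favour of XBJ. On this scale resumed NIV adds to the intubated patient's burden instead of changing what a short time means.

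**The case against.** **The analysis plan may settle it.** How to treat an event that interrupts a secondary outcome is often left to that plan, which is announced but not shown. A reader might infer that the trial has no rule at all; the documents do not support that, and it can be said only of this article. What remains is that the article itself fixes raw device durations and a t test on them. Counting intubated patients as not free of NIV would change that outcome rather than fill in a detail. The imputation sentence does not help, because an NIV time cut short is observed, not missing.

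**The direction is not fixed.** A reader might infer that XBJ must look worse if it works. That is too strong. Steps 3 and 4 show that the sign depends on NIV use before intubation and after extubation, and the article gives neither. A true reduction of NIV time by XBJ would also offset the shift.

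**The 15.2% and 4.7% are intubation rates, not NIV-failure rates.** The 15.2% comes from a routine-treatment group that was compared with early NIV plus routine treatment. The article also lists indications for intubation that do not depend on NIV. The full shift therefore needs the stated assumption that every intubated patient was first on NIV.

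**High-flow and oxygen therapy.** One might extend the argument to all the noninvasive durations. For high-flow oxygen the same direction is only plausible. For oxygen therapy it is not established, since intubated survivors may need oxygen for longer overall.

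**The pattern would be visible.** Invasive ventilation time is in the same item and would move with the intubation rate, so a careful reader could reconcile the results. No success criterion rests on NIV duration. Both points are fair and limit the weight of the concern, but the article states no joint reading.

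**Conclusion.** The concern holds in a limited form. As stated, NIV duration mixes recovery with the primary failure event, and a t test on the raw values can be biased against a drug that prevents intubation. Under the protocol's assumed 10.5-point reduction, with equal NIV need, every intubated patient first on NIV and no NIV after extubation, the bias is about 0.3–0.8 days for assumed durations of 5–8 versus 0.5–2 days. It is smaller if some intubated patients never had NIV. It is zero when NIV resumed after extubation makes up the time lost, and reversed beyond that. A single rejection rate should not be quoted: two plausible settings gave 25% and 0.8% of trials significantly against XBJ. The primary outcome and the sample size are unaffected.

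**What to change.** In the article's Secondary outcome measures and Statistical analysis, or in the analysis plan before unblinding:

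- Make the between-arm comparison days alive and free of NIV or invasive ventilation to day 28. Count invasive days as not free, and give patients who die the worst value.
- Compare the arms by a rank test stratified by centre, in keeping with the centre-adjusted test chosen for the primary outcome.
- Report the four raw durations descriptively only, split by whether the patient was intubated.

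The cost is mainly analysis wording, since the four durations and 28-day mortality are already outcomes and follow-up runs to day 28. Start and stop dates of support and dates of death are needed to avoid double-counting days; the article does not show whether the case report form holds them. The downside is that the composite does not isolate use of each device, which is why the raw durations stay as description.
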